### Trial Status

Recruitment started in February 2026, with data collection expected to be completed by December 2028. This protocol reflects version 1.0, finalized in January 2026. At the time of submission (May 2026), 6 participants were enrolled.

### Digital Components

The bTF-CBT-C will use the CE-marked Amni web-based application [38] to deliver psychoeducation, digital exercises, and weekly self-report measures. Participants will access the application on their own smartphones or tablets. For example, adolescents and caregivers may engage with short films and guided audio-based exercises such as soothing rhythm breathing. They may also complete interactive self-compassion exercises that involve reflecting on self-critical thoughts or participate in brief gamified quizzes and tasks to reinforce learning and engagement. The application also includes ratings after exercises to capture engagement and perceived helpfulness. It collects symptom, process, and engagement data through secure, encrypted channels, providing real-time feedback to the clinical team. Screenshots from the application are provided in Multimedia Appendix 2.

Videoconferencing sessions will be conducted using GDPR-compliant platforms (Visiba Care and Platform24), integrated into routine clinical workflows. Technical support will be available through the clinic to assist participants with login issues, navigation, or other technical challenges related to digital components.

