Adverse events (youth, caregiver + therapist)			✓	✓	✓
Primary outcomes (acceptability)					
Satisfaction (youth + caregiver)				✓	
Therapeutic alliance (youth, caregiver, therapist)^d^			✓	✓	
Digital treatment evaluation (youth + caregiver)^d^			✓		
Exercise evaluation^d^			✓		
Qualitative interviews			✓	✓	✓
Exploratory and clinical outcomes					
PTSD^e^ symptoms (CATS-2^f^, CRIES-13^g^)	✓		✓	✓	✓
Dissociation (DSQ-12^h^)	✓			✓	✓
Self-compassion (CEASY-SE^i^)	✓		✓	✓	✓
Emotion regulation (DERS-16^j^)	✓			✓	✓
Depression/anxiety/suicidality (MADRS-Y^k^, RCADS^l^)	✓		✓	✓	✓
Progression criteria					
Recruitment ≥60%	✓				
Retention ≥70%			✓	✓	✓
Acceptability ≥4/5				✓	
Data completeness ≥80%			✓	✓	✓

a SPIRIT: Standard Protocol Items: Recommendations for Interventional Trials.

b bTF-CBT-C: blended trauma-focused cognitive behavioral therapy with compassion.

c TF-CBT: trauma-focused cognitive behavioral therapy.

d Repeated mechanism/process measures (eg, therapeutic alliance, digital treatment evaluation, exercise evaluation, shame visual analogue scale, Trauma-Related Shame Inventory/Trauma-Related Guilt Inventory) are collected throughout the stabilization and trauma phases. A detailed full schedule table with all weekly/mid-module assessments (T0-T9) is provided in Multimedia Appendix 1.

e PTSD: posttraumatic stress disorder.

f CATS-2: Child and Adolescent Trauma Screen, version 2.

g CRIES-13: Children’s Revised Impact of Event Scale, 13-item version.

h DSQ-12: Dissociative Symptoms Questionnaire, 12-item version.

i CEASY-SE: Compassionate Engagement and Action Scale for Youth – Swedish Version.

j DERS-16: Difficulties in Emotion Regulation Scale, 16-item version.

k MADRS-Y: Montgomery-Åsberg Depression Rating Scale for Youth.

l RCADS: Revised Child Anxiety and Depression Scale.

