### Acceptability

#### Overview

Acceptability will be assessed using multiple indicators capturing participants’ and caregivers’ perspectives on the intervention and study procedures. Measures will include treatment satisfaction, therapeutic alliance (youth, caregiver, and therapist versions), ratings of digital treatment usability and engagement, and evaluation of individual exercises. In addition, qualitative interviews with adolescents, caregivers, and therapists will explore perceived helpfulness, burden, and acceptability of the blended format.

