#### Process and Mechanism Measures

Weekly and mid-module process measures (eg, alliance, digital engagement, exercise evaluations, and mechanisms related to shame and guilt) will be summarized descriptively and explored in relation to symptom patterns.

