### Progression Criteria

Progression to a fully powered noninferiority RCT will be determined based on predefined feasibility criteria established a priori, in accordance with CONSORT recommendations for pilot and feasibility studies. The pilot trial will be considered feasible to progress if the following thresholds are met: (1) recruitment: ≥60% of eligible participants enroll; (2) retention: ≥70% of enrolled participants complete the postintervention assessment; (3) acceptability: mean ratings of ≥4/5 from adolescents and caregivers on satisfaction and usability measures; and (4) data completeness: ≥80% of planned data points are collected across core assessment points.

These thresholds are consistent with feasibility patterns observed in comparable interventions. For example, blended trauma-focused cognitive therapy trials have reported high retention (approximately 88%) and strong satisfaction ratings (approximately 4.5/5), as in routine psychiatric care [58]. Similarly, digital PTSD interventions for youth have used recruitment, adherence, and retention as primary feasibility markers, with retention typically ranging from 70% to 90% [59]. Additional digital trauma-focused programs for adolescents and young adults report comparable feasibility patterns [12]. Together, these findings support the feasibility thresholds selected for the present pilot trial.

These criteria will guide decisions regarding whether the intervention and trial procedures are sufficiently feasible and acceptable to proceed to a fully powered trial. If one or more thresholds are not met, the research team will review barriers and determine whether procedural, methodological, or intervention-specific modifications are required before advancing to the next phase.

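### As written, alliance, digital treatment and exercise ratings can reach the clinical team during treatment; nothing withholds them, and the data-access statement is not reconciled with the feed

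*Protocol article*

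**What the plan says.** Digital Components describes the app as part of the experimental arm: "The bTF-CBT-C will use the CE-marked Amni web-based application [38] to deliver psychoeducation, digital exercises, and weekly self-report measures". It then describes where the data go: "It collects symptom, process, and engagement data through secure, encrypted channels, providing real-time feedback to the clinical team". No measure is exempted from that sentence. The same section says that the app takes ratings after exercises.

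Two places say what counts as process data. Footnote d of Table 1 (Study Design) reads "Repeated mechanism/process measures (eg, therapeutic alliance, digital treatment evaluation, exercise evaluation, shame visual analogue scale" and continues with shame and guilt inventories. Process and Mechanism Measures has "Weekly and mid-module process measures (eg, alliance, digital engagement, exercise evaluations, and mechanisms related to shame and guilt".

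The Acceptability overview makes the same instruments acceptability outcomes: "Measures will include treatment satisfaction, therapeutic alliance (youth, caregiver, and therapist versions), ratings of digital treatment usability and engagement, and evaluation of individual exercises". Table 1 places them under its primary outcomes heading. Of the quantitative acceptability ratings, Progression Criteria uses "mean ratings of ≥4/5 from adolescents and caregivers on satisfaction and usability measures".

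On access, Ethical Considerations says that identifiable data are open to authorized research team members alone. Safety Procedures says that risk reports alert the clinical team and that a clinician then contacts the family.

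**The concern.** A rating that the respondent believes will be read by the person or team being rated tends to be kinder, and a dissatisfied respondent may leave it blank. Adolescents in trauma treatment and their caregivers depend on the therapist, so the pressure is real. Here the ratings concerned are primary outcomes of a trial whose main purpose is to judge feasibility and acceptability. Ratings that drift upward, or go missing selectively, make the intervention look more acceptable than it is, and the decision to progress rests partly on those ratings.

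There is also a question of what families are told. If the access sentence in Ethical Considerations reaches the participant information unchanged, a family could believe that its answers go to researchers only, while the clinical team can see them.

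**Working it through.** The protocol gives no figure on this point, so there is nothing to reproduce. The check is to set the places side by side.

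1. **What is sent.** Digital Components sends process data, among others, to the clinical team in real time, with no exception.
2. **What process data are.** Footnote d names alliance, digital treatment evaluation and exercise evaluation. Process and Mechanism Measures names alliance and exercise evaluations again, and digital engagement in place of the digital treatment evaluation.
3. **What role the measures have.** The table below takes each one in turn. Satisfaction is included for contrast.

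| Measure | What it rates | Named as process measure | Completion in the app stated | Control-arm counterpart | In progression criterion |
|---|---|---|---|---|---|
| Alliance (youth and caregiver forms) | Goals, tasks and bond with the therapist | Yes, in both places | No | Likely, since Table 1 does not limit it to one arm; channel and access not stated | No |
| Digital treatment evaluation | The web-based components | Yes, in footnote d | Not explicitly | No web content described | Yes, read as the usability measure |
| Exercise evaluation | Exercises of the web-based phase | Yes, in both places | Nearly: the app takes ratings after exercises | No web content described | No |
| Satisfaction | Treatment as a whole, at T2 only | No | No | Not spelled out | Yes |

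4. **Whether anything withholds the ratings.** No section does. The nearest text is the access sentence in Ethical Considerations. It cannot literally cover the feed. Under Safety Procedures a clinician acts on an individual report and contacts that family, so the clinical team must be able to identify the respondent. The sentence might be meant for the research database only, or treating clinicians might count as authorized research team members. Neither is stated, and neither would keep the ratings from the therapist.
5. **What follows.** Steps 1, 2 and 4 together let alliance, digital treatment and exercise ratings reach the treating side during treatment. From the table, only alliance among the three rates the therapist, and only the digital treatment evaluation enters the progression criterion. No single measure is shown to do both and also to be in the feed.
6. **Size.** The documents give nothing from which to estimate a shift. If one assumes a shift of 0.2 to 0.5 points, a true mean of 3.8 would be read as 3.8 + 0.2 = 4.0, and a true mean of 3.5 as 3.5 + 0.5 = 4.0. That only restates the assumption. It also does not carry over to the digital treatment evaluation, whose items run from 0 to 4, so that 4 is the ceiling. No size is claimed.
7. **Timing.** Trial Status reports 6 enrolled in May 2026, out of a target of 40. That left 40 − 6 = 34 participants, or 34/40 = 85%, whose ratings could all be collected under an amended rule.

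**The case against.** The strongest reply is that disclosure is inferred. Digital Components speaks only in general terms. It does not say that alliance forms are completed in the app, that individual answers are displayed, or that the clinical team includes the therapist being rated. The lists in footnote d and in Process and Mechanism Measures are given as examples, and the detailed schedule is in an appendix that is not shown. Field-level viewing rights are the kind of operational detail an article leaves to the full protocol. This stands as a limit on how strongly the point can be put. It does not remove the point, because the article states a data flow without exception and also an access rule that does not fit it.

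A second reply is that the digital treatment and exercise evaluations rate an app and exercises, not a person. That is correct, and the pressure on those answers is weaker. It is not absent, since the readers are the team delivering the treatment.

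A third is that interviews with youth, caregivers and therapists give another view of acceptability, and that the Discussion already acknowledges expectancy and performance bias from the lack of blinding. Both help interpretation. Neither addresses who reads the ratings.

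A fourth is that clinicians have good reason to see app data, and that the protocol lets symptom severity and engagement guide adaptations. This stands in full, and the symptom, engagement, safety and adverse event feed should not be cut.

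**Conclusion.** The point holds in a limited form. As written, the protocol allows three primary acceptability measures to reach the clinical team in real time, does not withhold them, and does not square this with its own access statement. The likely direction is toward more favorable ratings. The exposure is most direct for alliance and possible for usability. The size is unknown. The conclusion assumes that process data in Digital Components means what the two later lists say it means, and that the clinical team includes or informs the treating therapist.

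Several stronger readings are tempting, and the documents do not support them:

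- A reader might infer that exposure in the experimental arm only is a stated fact. The app is described for bTF-CBT-C, but how control-arm alliance forms are collected and who sees them is not said. A difference between arms is plausible for alliance. For the other two measures there is no control-arm counterpart described, so no comparison to bias.
- A reader might infer that the progression decision rests on ratings of the therapist disclosed to the therapist. Alliance is outside the criterion, usability does not rate the therapist, and satisfaction is collected at T2 only and is not named as a process measure.
- A reader might infer that the symptom feed is a hidden co-intervention. It is openly described as part of the app that the experimental arm uses. The most that can be said is that the list of defining ingredients under Experimental Arm does not name it.

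This is a cheap improvement worth making now. It does not invalidate the design.

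**What to change.** - In Digital Components, state that youth and caregiver alliance ratings and digital treatment evaluation ratings go to research staff only and are hidden from the treating therapist until that participant's treatment has ended.
- Apply the same rule to alliance forms in both arms, whatever the channel in the control arm, and say what that channel is.
- Tell families, before they rate, who will see which answers.
- Reconcile the access statement in Ethical Considerations with Safety Procedures and Digital Components, so that it says which identifiable data the clinical team sees.
- Leave the symptom, engagement, safety and adverse event feed unchanged. If it is meant as an ingredient of bTF-CBT-C, name it under Experimental Arm.
- Exercise ratings may stay visible if they guide therapist support. In that case, state the visibility when they are reported as acceptability data.

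The cost is a change to viewing permissions in the app, a line of participant information and short text edits. The downside is that therapists lose sight of alliance and usability ratings while treatment is running. Ratings collected before the change should be identified as such in the report.

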### Recruitment and Randomization

Participants will be recruited through child and adolescent psychiatry clinics in the regions of Norrbotten and Västerbotten. Clinicians or research staff will provide information about the study to potentially eligible adolescents and caregivers during routine clinical contacts, after which interested families will be invited to undergo eligibility screening and informed consent.

Following completion of baseline assessments, eligible participants will be randomized in a 1:1 ratio to either bTF-CBT-C or standard TF-CBT. An independent researcher not involved in recruitment or treatment will generate a computer-based randomization sequence using permuted blocks (block size=4) to maintain balance between study arms. Randomization will be stratified by geographic region to account for contextual differences between sites.

Allocation will be concealed using sequentially numbered, sealed, opaque envelopes prepared by the independent researcher. Envelopes will be opened only after baseline assessments are finalized. Due to the nature of psychological treatment, therapists and participants cannot be blinded to group assignment; however, outcome assessors will remain blinded whenever feasible to minimize assessment bias.

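### A single published block size of 4 within region, with open treatment and clinic-based recruitment, lets someone who knows all earlier allocations in a region deduce up to a third of assignments

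*Protocol article*

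**What the plan says.** All the design facts stand in Recruitment and Randomization. The allocation list is a "computer-based randomization sequence using permuted blocks (block size=4) to maintain balance between study arms". The ratio is fixed: "eligible participants will be randomized in a 1:1 ratio to either bTF-CBT-C or standard TF-CBT". The strata are regional: "Randomization will be stratified by geographic region to account for contextual differences between sites". Two regions are named: "Participants will be recruited through child and adolescent psychiatry clinics in the regions of Norrbotten and Västerbotten".

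For concealment, the section states "Allocation will be concealed using sequentially numbered, sealed, opaque envelopes prepared by the independent researcher", and it has the envelopes opened only once baseline is complete. The list is made by a researcher who neither recruits nor treats. On blinding it says "therapists and participants cannot be blinded to group assignment", and adds that "outcome assessors will remain blinded whenever feasible to minimize assessment bias". On who approaches families: "Clinicians or research staff will provide information about the study to potentially eligible adolescents and caregivers during routine clinical contacts".

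The Setting section places screening, recruitment, assessment and treatment in the same clinics. Sample Size gives 40 participants, 20 per arm. Trial Status gives 6 enrolled at submission in May 2026, with recruitment continuing. The article mentions neither a varying block size nor central allocation.

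**The concern.** A block of four at 1:1 must end with two participants in each arm. Once one arm has used both its places, the rest of the block is known. Opaque envelopes hide their contents, but they do not stop this deduction. It needs only the block size, which the article publishes during recruitment, and the earlier allocations, which open treatment can reveal.

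The arms differ in ways that could shape staff preferences. The control arm is delivered in person at the clinic, the experimental arm mainly by video, and travel distance is central to the trial's rationale. Someone who foresees the next assignment could influence whether or when a family is approached, or how judgment-based exclusions (for example, unstable living conditions) are applied. All of this happens before the envelope is opened.

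At stake are baseline comparability and the arm-level descriptive figures for retention, adherence and adverse events. If eligible families are discouraged, the pooled recruitment rate is affected too, and that rate is a progression criterion.

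**Working it through.** The protocol gives no predictability figure, so there is none to reproduce. Inputs: block size 4, ratio 1:1 and two regional strata (Recruitment and Randomization); 40 participants (Sample Size); 6 enrolled at submission (Trial Status).

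**One block.** There are six equally likely sequences, three of which mirror the other three. The observer knows the earlier allocations in the block and always guesses the arm with more places left. A tie scores 0.5.

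| Sequence (and its mirror) | Places known with certainty | Expected correct guesses |
|---|---|---|
| AABB (BBAA) | 3rd and 4th: 2 | 0.5 + 0 + 1 + 1 = 2.5 |
| ABAB (BABA) | 4th: 1 | 0.5 + 1 + 0.5 + 1 = 3 |
| ABBA (BAAB) | 4th: 1 | 0.5 + 1 + 0.5 + 1 = 3 |

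- Chance of certainty by place: 0, 0, 1/3, 1.
- Certain share: (2 + 1 + 1)/3 = 4/3 per block, and (4/3)/4 = 33.3%.
- Best-guess success: (2.5 + 3 + 3)/3 = 2.833 per block, and 2.833/4 = 70.8%, against 50% by chance.

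**All 40 participants, by regional split.**

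- Both regions end on a full block (for example 20/20): 10 × 4/3 = 13.33, or 33.3%.
- Both end two places into a block (for example 22/18): 9 × 4/3 + 0 = 12.00, or 30.0%.
- One ends one place in and the other three places in (for example 21/19): 9 × 4/3 + 1/3 = 12.33, or 30.8%.

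**The 34 left at submission**, assuming that the 6 enrolled had been randomized and nobody since. The first 6 contain 1/3 + 1/3 = 0.67 expected certain allocations if split 3/3 by region, and 4/3 = 1.33 if split 4/2, 5/1 or 6/0. The remainder is therefore between 12.00 − 1.33 = 10.67 and 13.33 − 0.67 = 12.67, or about 11 to 13.

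**Effect of varying the block size.** Results are from 20,000 simulated lists of 20 per region. The observer knows the set of sizes and the full regional history, but not where blocks begin and end.

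| Block sizes | Known with certainty | Best guess correct |
|---|---|---|
| 4 only | 33.3% | 70.8% |
| 2 and 4 | 10.3% | 71.9% |
| 4 and 6 | 5.8% | 68.5% |
| 2, 4 and 6 | 3.7% | 69.6% |
| 4, 6 and 8 | 2.4% | 67.1% |

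Varying the size removes most of the certain knowledge. It hardly changes the success of an informed guess, and with sizes 2 and 4 that success rises slightly.

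**Balance.** An unfinished block of 4 can leave a region 2 apart, so two regions can be 4 apart (22/18). An unfinished block of 6 can leave a region 3 apart, so two regions can be 6 apart (23/17).

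**The case against.** The strongest reply is that the document does not show that recruiters hold the knowledge this deduction needs. It says that therapists and participants are unblinded and that clinicians or research staff inform families. It does not say that recruiters know the ordered allocations of a whole region. Strata are regions, each region may have several clinics, and certainty requires every earlier allocation in the current regional block. This stands: 33% is an upper bound, and staff at one clinic would know less.

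A second reply concerns consequences. A reader might infer that biased treatment-effect estimates pass into the noninferiority trial. The document does not support that. Quantitative Analysis uses the models descriptively, without testing. Results and Discussion carry forward mainly variability and feasibility. The thresholds under Progression Criteria are not set by arm. Delaying a family so that it falls in the other arm leaves pooled recruitment unchanged; only discouraging an eligible family lowers it. This also stands, and it limits the harm to baseline comparability, arm-level descriptive figures and possibly pooled recruitment.

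Third, there are real safeguards: an independent list-maker, sealed envelopes, opening after baseline, and eligibility based on a structured interview and a score cutoff. The motive to steer high-risk adolescents is weaker than it looks, because the experimental arm also gives priority to in-person sessions when risk is elevated. These points lower the risk, but none prevents deduction from past allocations. Preferences linked to distance remain plausible.

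Finally, varied blocks barely change guessing success, and changing a list during recruitment takes some care. Both are true, and both are counted in the verdict and the fix.

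**Conclusion.** The point holds as a bounded weakness that is cheap to reduce. With one disclosed block size of 4 per region, a fully informed observer could know up to 33% of allocations with certainty. That is 30% to 33% over the trial, and at most about 11 to 13 of the 34 left at submission. These figures assume knowledge of the block size and of every earlier allocation in the region. The count for the 34 also assumes no randomization after submission, and the number remaining now is not in the document.

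A reader might go further and infer that recruiters do know a third of the assignments, or that allocation has been manipulated. The document supports neither: it does not describe what recruiters see, and nothing in it suggests misconduct. Nor is any hypothesis test at risk, because none is planned. What remains is an avoidable opening for selective approach or timing in a small open trial whose arm-level feasibility figures will be read descriptively.

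**What to change.** For participants not yet randomized, the independent researcher should:

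1. complete or close the current block in each region;
2. generate the rest of each regional list with randomly varied block sizes, for example 4 and 6;
3. replace the unopened envelopes;
4. keep the sizes from recruiting staff and out of public documents until recruitment closes;
5. record the change and its date as a protocol amendment.

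Completing the current block preserves balance but leaves its remaining places as predictable as now. Closing it does the reverse.

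With sizes 4 and 6, certain knowledge among later allocations falls from about 33% to about 6%, while best-guess success stays near 68% to 69% instead of 71%. The amendment should therefore claim only that certainty is largely removed, not that guessing is prevented.

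The cost is a new list, new envelopes, a short amendment to version 1.0, and slightly more possible departure from 20/20. If the current block is completed first, the worst case from unfinished final blocks is 23/17 instead of 22/18.
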